### Statistics and data analysis

#### Sample size calculations

##### Main study

The rate of lung cancer was 187/100,000 per year for patients aged 50–74 in Scotland 2008 which is higher than many other similar countries [23]. Deprivation is associated with a significantly higher risk of lung cancer. Living in the most deprived quintile is associated with an increased risk of 1.8 times compared to the middle quintile of deprivation; this gives an estimated annual lung cancer rate of 336/100,000 among the practices taking part in the study. A high risk group within this population will be selected using similar entry criteria (outlined above) as the Mayo screening study which had a 2% prevalence rate of lung cancer and a further 2% incidence rate over the following 5 years [35]. The baseline rate of late stage presentation for the particular high risk population envisaged in this study is uncertain, as is the size of the reduction in late stage presentation likely to be achieved through use of EarlyCDT®-Lung Test. Using an estimated late stage presentation rate of 1,200/100,000 per year in the control arm i.e. 2.4% over the 2-years follow-up period, provides 85% power at 5% significance (two-sided) to detect an estimated reduction of 35% in late stage presentation rate in the intervention arm i.e. as low as 780/100,000 per year or 1.56% over the 2-years follow-up period. This corresponds to an estimated event rate over the 24 months of follow-up of 120 events in the control arm and 78 events in the intervention arm and implies a required sample size of 5,000 per arm i.e. a total of 10,000 participants.

The anticipated 35% reduction in event rate between the control arm and the intervention arm was justified by current estimates of the capability of the test to identify cases together with current estimates of the sensitivity of CT scanning (67%). The assumed event rate in the study participants of 1.2% per year was an estimate and the sample size would be modified if the observed event rate proves to be markedly different, acknowledging the a priori possibility that we will employ a prospective adaptive design. No Interim analysis of efficacy is planned.

The sample size calculations are based upon standard methods for time to event data using the c power function in R and st power exponential procedure in Stata and assuming exponential survival [34, 36]. They were also confirmed using standard approaches for detecting a change in binomial probabilities, and confirmed using approaches to detect a change in Poisson rates (with essentially identical results as loss to follow up is expected to be low due to completeness of Scottish Morbidity Register data).

The study aims for a short recruitment period and so no allowance has been made for accrual. With such an allowance, say to 1 year, the power will increase to 91% to identify a 35% reduction provided the minimum follow up period of 2 years is observed.

The initial assumptions of the rate of late stage presentation rate of 1,200/100,000 per year among the study participants was too optimistic and in January to May 2015 investigations were carried out to inform an increase in the sample size. Baseline information on the 8639 participants recruited to March 2015 (18 months from first randomisation) was used to derive an estimate of lung cancer risk based upon the Spitz Model. A number of variables in this model were not recorded in the study data base and low risk values were used in the risk calculation implying that the risk estimates should be underestimates. This suggested that the with 10,000 participants the rate of lung cancer would be expected to be around 680/100,000 and 540/100,000 for stage T3/T4/Unknown lung cancer using ISD cancer statistics figures of 80% lung cancers in Scotland are late stage. A sensitivity analysis around the missing data assumptions suggests that a late stage rate of around 600/100,000 may not be unreasonable, though is likely to be at the upper limit.

Using an assumption of 600/100,000 for late stage lung cancer, increasing the sample size to 12,000 [37], and acknowledging that recruitment is over a 2 years period the study has a power of 80% to detect a 35% reduction associated with the use of the EarlyCDT-Lung test to identify cases, provided that analysis takes place after all randomised patients have been followed up for 2 years. While an 80% power is at the lower end of acceptable powers this is the power level which has been used in a number of lung cancer screening trials.

The power of the study is sensitive to the assumptions about the rate of late stage cancer and the recruitment rate. A power in excess of 90% could only realistically be achieved by recruiting 15,000 patients or by changing the primary endpoint to 3 years post randomisation for all patients. If the recruitment phase extends past 2–2.5 years to recruit 12,000 participants then the power will increase slightly to 83%.

##### Substudies

For the follow-up analysis of behavioral and psychological outcomes, 200 participants in each group (test-positive, test-negative and the control arm) will allow detection of a mean difference of 3.00 (SD 15.04 (unpublished data comparing pre and post prostate biopsy scores from the ProtecT prostate cancer study)) in the Impact of Events Scale between baseline and follow up measurements. (http://www.ncbi.nlm.nih.gov/pubmed/21047592) This study reported within each group and a mean difference of 4.2 (SD 15.04), between each of the test groups and the control arm with 80% power and 2-sided 5% significance level. Assuming 80% of participants are current smokers, this will provide 80% power at 5% significance level to detect a 13% point difference in the prevalence of smoking between each of the test groups and the control arm (i.e. from 80 to 67%) To allow for attrition, we will recruit 300 participants in each group.

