#### Secondary

numbers at 24 months after randomisation, in the different stages at diagnosis (III/IV/U/other) in the intervention arm and the control arm;difference, after 24 months, between costs and outcomes between the intervention arm and in the control arm and cost-effectiveness of the test compared to standard practice;differences, after 24 months, of lung cancer mortality, all-cause mortality and cancer-specific mortality rates between the intervention arm and in the control arm;differences, after 5 and 10 years, of long-term future mortality rates in the intervention arm and in the control arm;differences, after 24 months in (i) the number of patients with stage III, IV or unclassified lung cancer at diagnosis in the test-positive group and those in the test-negative group and (ii) stage at diagnosis in the test-positive and test-negative group;difference between the test-positive, test-negative groups and the control arm at 1, 3, 6, and 12 months in scores for EQ5D [29], Positive and Negative Affect Schedule [30], revised Illness Perception Questionnaire adapted to refer to lung cancer and lung cancer risk [31], Lung cancer risk perception, Health anxiety subscale of Health Orientation Scale [32], the Adapted Lung Cancer Worry Scale [33] and Impact of Events Scale [34] (for the test-positive group, the test-negative group only) and differences in smoking behaviour and health service use. Long-term scores for the same outcomes for the test-positive group at 18 and 24 months;difference in incidence at 24 months, and after 5 and 10 years, in other clinical measures such as Cerebrovascular disease, Chronic Obstructive Pulmonary Disease, hospital stays, and outcomes identified through the Scottish Morbidity Record (SMR) linkage in the intervention arm and in the control armnumbers in all groups at 24 months (test-positive, test-negative and control) undertaking subsequent investigations such as chest X-ray, CT and bronchoscopy (Table 1)

**Table 1 Tab1:** Data Collection Timeline

Assessment/Procedures	Timeline (± 2 weeks)				
	Visit 1 (~30-45mins)		Visit 2 (~30mns)	➢ *EarlyCDT Positive Test Participants may visit or call.* ➢ *EARLY CDT Negative Test Participants may attend for further information/advice only.*	
*Informed Consent*	X				
*Inclusion/Exclusion Criteria*	X				
• *Review/Record only Relevant Medical History relating to IC/EC*	X				
• *Review/Record Relevant Medications* • *Relating to IC/EC*	X				
*Blood Sample*	X				

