### Data collection & management

#### Data collection

All research blood samples will be transported to the University of Nottingham for processing, and then transported to the US for Test processing by Oncimmune. All samples will be stored under custodianship as per UK Biobank guidelines [40]. Sample Analysis and Chain of Custody Plans are documented in the Study Operations Manual. The participant’s medical notes (GP and hospital) paper or electronic will act as source data for relevant past medical history, subsequent medical conditions, hospital admissions and diagnostic reports.

Psychological and behavioural data will be collected on the first 10,000 participants through a baseline questionnaire administered during Visit 1. Follow-up data will be collected between 1 and 12 months on subsets of the intervention and control arms and at 18 and 24 months for the EarlyCDT®-Lung Test-positive group. Data collected at baseline will include the EQ5D, Hospital Anxiety and Depression Scale, Positive and Negative Affect Schedule, revised Illness Perception Questionnaire adapted to refer to lung cancer and lung cancer risk, lung cancer risk perception, items from the Health Orientation Scale, the adapted Lung Cancer Worry Scale, smoking behaviour and demographic details. Follow-up questionnaires include the same measures, plus health service use and Impact of Events Scale and health service use for those who had the test. The Hospital Anxiety and Depression Scale is not included in follow-up questionnaires and the EQ-5D is not included in the 3 months follow-up questionnaire.

All participants in the positive group will be approached with the recruitment aim of 300 from this group. The TCTU will use an electronic randomisation tool to randomly sample patients from the test-negative group and control arm, stratified by the two study centres. Twenty-one individuals will be sampled each week and invited to complete follow-up questionnaires with an aim of recruiting 300 from both groups (based on an anticipated response rate of 67%).

Participants who receive a diagnosis of lung cancer will not be followed up subsequent to receiving the diagnosis.

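### Two of the three stated bases for the substudy size are Impact of Events Scale contrasts that the data collection plan cannot supply; the smoking basis still supports the group size

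*Protocol article*

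**What the plan says.** The sample size section of the protocol article (Substudies) gives three bases for the psychological and behavioural follow-up.

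- Within group: "200 participants in each group (test-positive, test-negative and the control arm) will allow detection of a mean difference of 3.00", with SD 15.04, "in the Impact of Events Scale between baseline and follow up measurements".
- Between groups: "a mean difference of 4.2 (SD 15.04), between each of the test groups and the control arm with 80% power", at a two-sided 5% level.
- Smoking: 80% power for a fall in prevalence from 80% to 67% between each test group and control.

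Recruitment is raised to 300 per group for attrition.

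Two other sections say who completes the scale and when. The Secondary outcomes list, comparing the three groups at 1, 3, 6 and 12 months, attaches a restriction to this one instrument: "Impact of Events Scale [34] (for the test-positive group, the test-negative group only". Data collection does not name the scale among the baseline instruments. It then describes the follow-up questionnaires as the same measures "plus health service use and Impact of Events Scale and health service use for those who had the test". Under Administration of the test, everyone gives blood but the test is run only for the intervention arm, so controls are not among those who had the test.

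**The concern.** A power statement describes a contrast that will be estimated. Here the first Impact of Events contrast needs a pre-test score and the second needs a score in controls, and the collection plan provides neither.

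The possible psychological harm of screening is a stated aim, and the comparison with an untested control arm is the one that bears on it most directly. If a psychological comparison with control turned out null, a reader of the Substudies paragraph could believe that it had 80% power for a named effect. No psychological scale collected in controls has such a statement.

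**Working it through.** **Inputs (Substudies).** n = 200 per group; SD = 15.04; change 3.00 within group; difference 4.2 between groups; two-sided 5%, 80% power (z = 1.960 and 0.842, sum 2.802); smoking 80% v 67%.

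**Step 1: the plan's own figures.**

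- Within group: 3.00 / (15.04/√200) = 2.82; power = Φ(2.82 − 1.96) = 80.5%. Required n = (15.04 × 2.802 / 3.00)² = 197.3, so 198.
- Between groups: 4.2 / (15.04 × √(2/200)) = 4.2 / 1.504 = 2.79; power = Φ(2.79 − 1.96) = 79.7%. Required n = 202 per group.
- With t distributions the powers are 80.2% and 79.6%.

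Both figures reproduce from their stated inputs. The fault is not numerical.

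**Step 2: can the contrasts be formed?**

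| Contrast on the Impact of Events Scale | Data needed | Planned? |
|---|---|---|
| Change from baseline, any group | Baseline score | No: not in the baseline list; added at follow-up |
| Each test group v control | Control score | No: tested participants only, in two sections |
| Test-positive v test-negative at follow-up | Follow-up score in both | Yes |
| Change between follow-up times, tested participants | Repeated follow-up scores | Yes |

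The two contrasts that were powered are the two that cannot be formed.

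**Step 3: the smoking basis.** Smoking behaviour is in the baseline list, is repeated at follow-up, and is not restricted to tested participants. With mean proportion 0.735:

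- Required n = [1.960 × √(2 × 0.735 × 0.265) + 0.842 × √(0.80 × 0.20 + 0.67 × 0.33)]² / 0.13² = 180 per group (195 with continuity correction).
- Power at 200 = Φ[(0.13 × √200 − 1.223) / 0.617] = Φ(0.997) = about 84%.

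So 200 evaluable, or 300 recruited with 200/300 = 66.7% retained, keeps a valid stated basis.

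**Step 4: what 200 per group gives on data that will exist.**

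- Any score collected in both groups: detectable difference = 2.802 × √(2/200) = 0.28 SD with 80% power, unadjusted for baseline.
- Impact of Events, test-positive v test-negative at follow-up: 0.28 × 15.04 = about 4.2 points, if that SD applies. If the true SD were 20% smaller or larger, purely as an illustration, this would be about 3.4 or 5.1 points.

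**The case against.** **The baseline list may not be exhaustive.** It is worded as what the data will include. But the next sentence adds the scale at follow-up, over and above the repeated measures, and only for those tested. Even with a baseline score, the contrast with control would still fail, because the Secondary outcomes list separately leaves controls out.

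**The 4.2 may not refer to this scale.** The sentence is garbled and does not repeat the scale's name. That half of the point is an inference, but a firm one: the SD is again 15.04 and no other scale is mentioned.

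**The substudy remains adequately sized.** This stands. A reader might infer that the substudy has no valid power at all, or that nothing is powered against control. The documents do not support either reading, because the paragraph covers behavioural as well as psychological outcomes and the smoking comparison with control is computable.

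**The scale still has uses.** This also stands. A reader might infer that test-positive v test-negative is the only Impact of Events analysis left. In fact tested participants complete it repeatedly, test-positives out to 24 months, and Proposed analyses plans multilevel models for repeated measurements. Only change from a pre-test baseline is lost.

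**Conclusion.** The point holds in a limited form. The stated 80% power for the two Impact of Events contrasts describes data that the protocol article does not plan to collect. The three sections contradict one another.

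The consequence is the loss of any stated power for a psychological score against control. The numbers of 200 evaluable and 300 recruited per group, the main trial's sample size and the primary outcome are untouched. That makes this a moderate correction to a power statement for secondary outcomes.

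The conclusion rests on reading the 4.2 as an Impact of Events difference. The 4.2-point figure for test-positive v test-negative also assumes that SD 15.04 carries over. It comes from scores before and after prostate biopsy, and the article does not say whether it is the SD of a change or of a single score.

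**What to change.** Reconcile the Substudies paragraph with the Secondary outcomes list and Data collection.

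1. Remove the Impact of Events claims for change from baseline and for difference from control.
2. Limit the Impact of Events power statement to test-positive v test-negative at follow-up: about 4.2 points with 80% power at 200 per group, with SD 15.04 labelled as an assumption taken from pre/post biopsy data.
3. State power against control on a psychological scale collected at baseline and follow-up in all three groups, such as the Positive and Negative Affect Schedule or the adapted Lung Cancer Worry Scale: 80% power for about 0.28 SD at 200 per group, unadjusted for baseline. The article gives no SD for these scales, so one is needed before this can be put in points. The Hospital Anxiety and Depression Scale cannot serve, because Data collection leaves it out of the follow-up questionnaires.
4. Keep the smoking statement.

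The cost is the wording of one paragraph, with no added participants, questionnaires or change in group size.

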### Proposed analyses

Characteristics of participants will be compared informally between treatment arms at baseline. The main analysis of the primary outcome will be intention-to-treat. Cox proportional hazards models which will be used to estimate the hazard ratio of the rate of late stage lung cancer in the intervention arm compared to the control arm. Participants who are lost to follow up will be censored. The models will adjust for age, gender smoking history, socioeconomic status and practice. If appropriate, random cluster effects will be included rather than fixed effects for practices. A similar methodology will be used for the secondary outcomes of comparisons of mortality rates. A subsequent analysis will compare the outcomes of those with a positive test in comparison to those in the intervention group with a negative test (primary contrast for this analysis) and those in the control group. Comparisons of proportions will be carried out using chi square tests. Fisher’s exact test will be used if the number of events is small.

Psychological and behavioral outcomes will be compared between the three groups (Test-positive, Test-negative and the control group) at baseline using analysis of variance (or non-parametric tests if there is evidence of non-normal distribution of scores) for continuous measures and *χ*
^2^ tests for categorical measures. Psychological (HADS Score) and behavioral measures will be described at each follow up time point and multilevel regression models will be used for analyses to take account of repeated measurements during follow up [38].

Poisson regression models, adjusting for follow up time if necessary, will be used to investigate the other clinical measures (secondary outcomes 7 and 8).

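### The analysis section plans to follow HADS over time although HADS is collected only at baseline, and the outcome list has EQ-5D at 3 months, when it is not collected

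*Protocol article*

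**What the plan says.** Three places in the protocol article bear on this.

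- **Proposed analyses.** After a baseline comparison of the three groups (test-positive, test-negative, control), the section turns to follow-up: "Psychological (HADS Score) and behavioral measures will be described at each follow up time point and multilevel regression models will be used". The stated purpose of the models is "to take account of repeated measurements during follow up". HADS is the only psychological score that this section names.
- **Data collection.** The baseline set is described first: "Data collected at baseline will include the EQ5D, Hospital Anxiety and Depression Scale, Positive and Negative Affect Schedule", followed by the remaining scales. Then comes a general rule, "Follow-up questionnaires include the same measures, plus health service use and Impact of Events Scale", the last of these only for people who had the test. Two explicit exceptions follow: "The Hospital Anxiety and Depression Scale is not included in follow-up questionnaires and the EQ-5D is not included in the 3 months follow-up questionnaire".
- **Outcomes, Secondary.** The psychological outcome is given as "difference between the test-positive, test-negative groups and the control arm at 1, 3, 6, and 12 months in scores for EQ5D". The list continues with the Positive and Negative Affect Schedule (PANAS), the revised Illness Perception Questionnaire, lung cancer risk perception, the health anxiety subscale, the adapted Lung Cancer Worry Scale and, for the two tested groups only, the Impact of Events Scale. HADS is not in the list.

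**The concern.** An analysis section should name variables that will exist. Here the one psychological score it names will have no follow-up values, and one outcome has a comparison time at which nobody will be asked the questions. Both are contradictions between current parts of the same document. They are not details that a condensed article leaves to a fuller one.

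The Discussion makes psychological harm and benefit from test results a stated aim of the study, and this substudy is where that is examined. Someone working from Proposed analyses would look for a repeated HADS score and not find it. Someone working from the outcome list would set up an EQ-5D contrast at 3 months with no data in it. Because HADS is not a listed outcome either, the analysis section and the outcome list also disagree about what is being measured.

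**Working it through.** No sample size, power or significance level is involved. The check sets the sections against each other and counts measurement times.

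**Inputs**

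| Measure | Listed secondary outcome? | Baseline (Data collection) | Follow-up (Data collection) | Role in Proposed analyses |
|---|---|---|---|---|
| HADS | No | Yes | None (explicit exception) | Named; described at each follow-up, repeated-measures models |
| EQ-5D | Yes, three groups at 1, 3, 6, 12 months | Yes | Not at 3 months (explicit exception) | Not named |
| PANAS, Illness Perception, risk perception, health anxiety, Lung Cancer Worry | Yes, three groups at 1, 3, 6, 12 months | Yes | Yes (general rule, no exception) | Not named |
| Impact of Events Scale | Yes, two tested groups only | Not in the baseline set | Yes, for those tested | Not named |

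**Step 1: HADS.** The three-group follow-up times are 1, 3, 6 and 12 months. HADS is collected at 0 of these 4. The test-positive group has further questionnaires at 18 and 24 months, and the exception is not limited to particular questionnaires, so the count there is 0 of 2. With a single baseline value per person there is nothing to describe at follow-up and no repeated measurement to model.

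**Step 2: can the general rule rescue HADS?** The rule that follow-up questionnaires repeat the baseline measures would cover HADS if it stood alone. The exception comes directly after it and names HADS. A specific exception overrides a general rule, so the conflict remains.

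**Step 3: EQ-5D.** Listed three-group times: 1, 3, 6, 12 months, which is 4. Times excluded by Data collection: 3 months, which is 1. Times with data: 4 − 1 = 3, namely 1, 6 and 12 months. This part rests on the outcome list against Data collection and does not depend on the HADS sentence.

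**Step 4: what remains analysable.** Five scale groups (PANAS, Illness Perception, risk perception, health anxiety, Lung Cancer Worry) are listed outcomes and are collected at baseline and at follow-up in all three groups. The planned multilevel models can be fitted to each. EQ-5D can be modelled at its three remaining times. The Impact of Events Scale can be compared over follow-up between the two tested groups. It has no baseline value and no control-arm values, so it cannot take the place of HADS in a three-group comparison, although the Substudies section bases its sample size on it.

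**The case against.** The strongest reply is that the HADS label is a stray parenthesis. The sentence speaks of psychological and behavioural measures in general, the paragraph opens in the same general terms, and the outcome list already gives every scale with its times. Because HADS is not a listed outcome, no listed outcome loses its analysis. For EQ-5D, the outcome list uses one shared set of times for several instruments, and Data collection states the exception openly. All of this stands, and it limits the consequence. It does not make either statement correct: no section reconciles either pair, and the parenthesis still names a score with no follow-up data.

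Two stronger readings are tempting, and the document does not support them.

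- A reader might infer that the psychological analysis as a whole cannot be run. Only the HADS part cannot. The multilevel models remain feasible for the listed scales and the behavioural measures.
- A reader might infer that the scales to be reported would be chosen after the data are seen. The outcome list already fixes the scales and their times, so no choice among them is needed. The section on data management also says that the statistical analysis plan, which is not shown here, will specify dummy tables linked to the outcomes. Selective reporting would be speculation.

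**Conclusion.** The point holds as two internal contradictions. HADS is to be described and modelled at follow-up, yet it has 0 follow-up measurements. The three-group EQ-5D comparison is listed at 4 times, of which 3 will have data. The conclusion takes the Data collection section as the correct account of what the questionnaires contain. That is reasonable, because it is the specific statement and both exceptions are explicit, but the sponsor should confirm it against the questionnaires.

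The reach is small: secondary outcomes only, in a substudy that aims for 300 people per group. The primary outcome and its power are unaffected. The text should still be corrected, because the statements are wrong as written, they concern a stated aim of the trial, and correcting them is cheap.

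**What to change.** 1. **Proposed analyses.** Replace the HADS label with the listed scales that are collected at baseline and follow-up in all three groups: PANAS, the revised Illness Perception Questionnaire, lung cancer risk perception, the health anxiety subscale and the adapted Lung Cancer Worry Scale. Add the Impact of Events Scale for the test-positive and test-negative groups only. Do not replace HADS with a single scale, because that would narrow the analysis below the listed outcomes.
2. **Model.** Include each scale's own baseline value as a covariate in its multilevel model where one is collected. The Impact of Events Scale has none. The gain in precision depends on correlations that the document does not give, so no figure is put on it here.
3. **HADS.** State that it is a baseline measure only.
4. **Outcomes, Secondary.** Give the three-group EQ-5D comparison at 1, 6 and 12 months.

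The cost is a few words in two sections and a covariate that is already in the baseline questionnaire. No new instrument, visit or questionnaire is needed. If the full protocol or statistical analysis plan repeats either statement, make the same change there.

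### The analysis text tests psychological and behavioural outcomes at baseline but does not name the participant's baseline value as a covariate in the follow-up models, though most of these outcomes are measured before randomisation and repeated

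*Protocol article*

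**What the plan says.** **Analysis.** Protocol article, Proposed analyses: "Psychological and behavioral outcomes will be compared between the three groups (Test-positive, Test-negative and the control group) at baseline using analysis of variance", with non-parametric tests as the alternative and chi-square tests for categorical measures. The measures are then described at each follow-up time, and "multilevel regression models will be used for analyses to take account of repeated measurements during follow up". No covariate is named for these models. The same section lists five adjustment variables for the primary Cox model: age, gender, smoking history, socioeconomic status and practice.

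**Data.** Data collection lists the baseline set: EQ-5D, HADS, PANAS, illness perception, lung cancer risk perception, Health Orientation Scale items, the Lung Cancer Worry Scale, smoking behaviour and demographics. "Follow-up questionnaires include the same measures, plus health service use and Impact of Events Scale", the last for those who had the test. HADS is not repeated, and EQ-5D is omitted at 3 months. Initial consultation places the questionnaire before randomisation, so baseline also precedes the test result.

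**Groups.** All test-positive participants are approached. The trials unit will "randomly sample patients from the test-negative group and control arm, stratified by the two study centres", with an anticipated response rate of 67% for those samples.

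**Size.** Substudies bases its calculation on "200 participants in each group (test-positive, test-negative and the control arm"), for "a mean difference of 4.2 (SD 15.04), between each of the test groups and the control arm" on the Impact of Events Scale "with 80% power and 2-sided 5% significance level". It also sizes on a within-group change of 3.00 from baseline to follow-up on that scale, and on smoking prevalence falling from 80% to 67%.

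**The concern.** The one between-group use of baseline that Proposed analyses states is a significance test, which does not do the work of adjustment. A non-significant result does not remove an imbalance, and a significant one triggers no stated action.

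This matters more here than in a comparison of randomised arms. Test-positive and test-negative are formed by the test result, and each of the three groups is further selected by who returns questionnaires. If responders in one group were already more worried, or smoked more, a follow-up contrast without baseline would show that difference as if the result had caused it. That argument needs no assumed correlation.

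The second cost is precision. The Abstract and Discussion make psychological and behavioural harm one of the trial's conclusions. Intervals wider than the collected data allow make it easier to miss a harm or a change in smoking and to read the result as reassurance.

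**Working it through.** **1. Reproduce the plan's figure.** Inputs from Substudies: n = 200 per group, difference 4.2, SD 15.04, two-sided 5%.

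- Standardised difference: d = 4.2/15.04 = 0.279.
- Power = Φ(d·√(n/2) − 1.96) = Φ(0.279 × 10 − 1.96) = Φ(0.83) = 79.7%.

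The stated 80% reproduces.

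**2. Add the baseline value at one follow-up time.** Adjustment multiplies the residual variance by (1 − r²), where r is the baseline to follow-up correlation. Power = Φ(d·√(n/[2(1 − r²)]) − 1.96). The article gives no r, so a range is assumed.

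| r (assumed) | 1 − r² | Power | Gain in points |
|---|---|---|---|
| 0 | 1.00 | 79.7% | – |
| 0.3 | 0.91 | 83.3% | 4 |
| 0.4 | 0.84 | 86.1% | 6 |
| 0.5 | 0.75 | 89.7% | 10 |
| 0.6 | 0.64 | 93.7% | 14 |
| 0.7 | 0.51 | 97.4% | 18 |

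The difference and SD belong to the Impact of Events Scale, which has no baseline. The table therefore shows what the same standardised difference would gain on a scale that does have one. It is not a result for the Impact of Events Scale.

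**3. Average of four follow-ups (1, 3, 6 and 12 months).** Assume a common correlation r among all times, baseline included. The variance factor for the mean is (1 + 3r)/4 unadjusted and (1 + 3r)/4 − r² adjusted.

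| r | Factors | Unadjusted | Adjusted | Gain in points |
|---|---|---|---|---|
| 0.3 | 0.475 → 0.385 | 98.2% | 99.4% | about 1 |
| 0.5 | 0.625 → 0.375 | 94.2% | 99.5% | about 5 |
| 0.7 | 0.775 → 0.285 | 88.7% | 99.9% | about 11 |

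At each r the gain is smaller than at a single follow-up time.

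**4. Smoking.** Take 80% baseline smokers (Substudies), 200 per group and an 8-point difference produced by extra quitting, which is 8/0.8 = 10 points more quitting among smokers. Quit and relapse rates are assumptions.

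- Unadjusted variance: [p₀(1 − p₀) + p₁(1 − p₁)]/n.
- Variance given baseline status: {0.8[q₀(1 − q₀) + q₁(1 − q₁)] + 0.2 × 2ρ(1 − ρ)}/n, with q the quit rate and ρ the relapse rate.
- 5% of controls quit, no relapse: p₀ = 0.76, p₁ = 0.68; standard error 0.0447 falls to 0.0265; power 43% to 86%.
- 15% quit, 10% relapse: p₀ = 0.70, p₁ = 0.62; standard error 0.0472 falls to 0.0379; power 40% to 56%.

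The direction is the same in both cases. The size is set by the assumed rates.

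**5. Which outcomes can use a baseline.** PANAS, illness perception, risk perception, Health Orientation items, the worry scale and smoking can, as can EQ-5D at the times it is collected. The Impact of Events Scale and HADS cannot.

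**The case against.** The strongest reply is that this is silence, not exclusion. The phrase about repeated measurements explains why the model is multilevel; it does not say baseline is left out. Covariates for secondary models are commonly left to the statistical analysis plan, which the article says will exist. This stands to the extent that the loss is conditional on the models being run as written. It does not dispose of the point, because the article does commit to a between-group test at baseline, and adjustment is a better use of the same data.

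A reader might infer that about 10 points of power are lost. The documents do not support that figure. It needs r = 0.5, which is not given. Reading 0.5 from the use of 15.04 for both the change and the between-group difference is weak, since Substudies does not say which kind of SD it is.

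A reader might also infer that baseline serves only for the significance test, or that smoking is to be compared as raw prevalence. Substudies sizes partly on a baseline to follow-up change, so baseline has another intended use there, though Proposed analyses describes no analysis of that change. The prevalence figures of 80% and 67% in Substudies are a sizing statement; behavioural measures fall under the multilevel models.

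Finally, no baseline difference between the groups is documented, and test-negative and control participants are sampled at random. That is fair: the bias is a risk, not a shown fact. Random sampling does not make a result-defined group comparable with the others, nor does it remove selection through response.

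**Conclusion.** The point holds as an improvement that should be made. As written, the analysis text tests baseline and does not say that the follow-up models adjust for it, although the data are in hand for most of these outcomes. If the models were run without it, contrasts between groups that are not randomised against each other would keep any pre-existing differences and give up precision.

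The size is illustrative: 4 to 18 points of power at one follow-up time for a standardised difference of 0.28, 200 per group and r from 0.3 to 0.7; about 1 to 11 points if four follow-ups are averaged under a common correlation. It rests on assumed correlations and on a standardised difference borrowed from a scale that has no baseline. The smoking gain rests on assumed quit and relapse rates. The text does not establish that power is lost or that bias is present.

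**What to change.** In Proposed analyses:

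- Replace the between-group significance tests at baseline with a descriptive table of the three groups.
- State that each multilevel model for a psychological or behavioural outcome includes the participant's baseline value of that outcome, plus study centre (the stratum for sampling test-negative and control participants) and age, sex and smoking history (the minimisation factors).
- For smoking, use baseline smoking status as the baseline covariate.
- For the Impact of Events Scale, which has no baseline, keep only the centre and minimisation covariates.

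The cost is wording. The covariates are already collected, and no further participants or questionnaires are needed. The small downside is that participants with a missing baseline item need handling, which the Missing data section already provides for through multiple imputation if necessary.
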